### Sample Size

A total sample size of 1188 (inflated by 10% for loss to follow up, n=594 in each arm) is needed to detect a 10% reduction of penile sexual events in the intervention group with 90% power with an alpha of .05. The control event rate is estimated at 60% based on previous studies in similar populations.

### Recruitment

Participants are recruited at the clinics where MMC services are offered in the greater Cape Town area. There are two roaming VMMC teams in the area offering services 4 days per week. The research assistants are divided between the teams and follow them depending on where they are on a set weekly schedule.

### Allocation

The randomization sequence will be generated by a biostatistician using a computer-generated table of random numbers. Assignment sequences will be placed in consecutively numbered opaque sealed envelopes ensuring allocation concealment. The study numbers are allocated consecutively as the patients come into the waiting area and written in the top corner of the envelope, which is handed to the participant.

### Blinding

This will be a single-blind RCT: data collectors, researchers, and analysts will all be blind to the patient’s allocation to study arm. The envelopes are numbered consecutively by the fieldworkers, and at the end of each recruitment day, the team sends a list of the participants’ study ID numbers, mobile numbers, and preferred language of messages to an office-based study administrator who has the group allocation master list. The study administrator then logs on to the HISP website and registers the mobile phone details of the intervention group, who start getting messages the next day. At no stage does the team in the field know the allocation of any study number, and at no stage does the study administrator come into contact with the participants or their personal information.

### Data Collection

Data is collected through self-administered paper and pen questionnaires offered in either English or Afrikaans. The consenting participants fill out the questionnaire while they wait for their HIV testing and preoperative counseling. They are asked to come back to the clinic for a follow-up visit after 6 weeks. HIV status will be collected (coded) from files if consent is given by the participant. Completed questionnaires are processed and captured at the office by the data capturer and stored in a locked room. The completed questionnaires are linked to the participants through their study numbers only and not the electronic health platform.

### Follow-Up Procedures

Participants return to the same clinic where they were recruited (or a nearby convenient public space) after 6 weeks for a follow-up visit consisting of a questionnaire. Based on many years of panel studies in the population, the team has developed the following mechanism for ensuring high retention: as part of the consent process, the participant will complete a contact form including his phone number and the names and phone numbers of two people close to him. He will also be given an appointment card that indicates the date of the 42-day follow-up visit. In the 6 weeks following surgery, participants are contacted with a brief phone call at 1, 3, and 5 weeks to remind them of their follow-up date and to reschedule if necessary. If a participant does not show up for the follow-up visit, contact is attempted up to 3 times in the following 2 weeks to reschedule. If the participant is reached but unable to reschedule, he is invited to complete a subsample of the follow-up questionnaire (10 questions) via the telephone. If he is not located, he is considered lost to follow-up.

### Analysis

#### Descriptive Analysis

Data will be analyzed using Stata 13 statistical software (StataCorp LP) according to the intention-to-treat principle. Descriptive statistics will be used to summarize the data. Continuous outcome variables will be tested for normality using descriptive statistics (eg, histograms, qq plots, and box plots). If normally distributed, continuous variables will be presented as means and standard deviations; if not, they will be reported as medians and interquartile ranges. Categorical data will be presented as proportions. An alpha of .05 will be considered statistically significant, and 95% confidence intervals will be reported where appropriate. Baseline prognostic variables and possible confounders will be compared between intervention and control groups using the appropriate univariate statistical methods. Clinical imbalances will be considered in further adjustment regression models.

#### Inferential Analysis

The primary outcome—occurrence of any homosexual or heterosexual penetrative intercourse at any time in the first 42 days after VMMC—will be compared between the intervention and control groups. The primary analysis will be to detect a difference in proportions using an unadjusted binomial test. Additionally, generalized linear regression models for the analysis of binary outcomes will be used to study the effects of the intervention as well as possible synergistic effects, taking potential confounders into account if necessary (eg, age, religion, marital status, education, employment, depression). The final covariate model will include all variables known to have a meaningful impact on bias in the estimate of the treatment effect. The covariate adjusted relative risk for treatment effect and 95% confidence interval will be reported. A covariate adjusted absolute risk difference for the effect of treatment and the 95% confidence interval will also be presented. In addition, we will report number needed to treat.

Secondary outcomes will be analyzed in the same manner as the primary outcome. A per-protocol compared to intention-to-treat sensitivity analysis will be performed on the primary outcome.

Missing primary outcomes will be assumed to be missing at random; however, if more than 15% of all primary outcomes that should be available for analysis are missing, a sensitivity analysis will be undertaken in addition to the primary missing at random analysis and results compared.

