### Other Substudies

There is a substudy embedded in the follow-up survey at 42 days which looks at how the study population reacts to the mobile system. The purpose is to evaluate the level of learnability and feasibility for the user in real life. This includes responsiveness to messages. Another study of nonresponse will be conducted comparing answers to a smaller number of questions (on exposure and outcome) of those lost to follow-up with those who remained in the cohort.

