## Results

Enrollment was completed on June 29, 2016. Follow-up of enrolled participants is ongoing. Loss to follow-up is under 10%. No interim analyses have been conducted.

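### The missing-data sensitivity analysis is tied to a 15% trigger that lies above the planned and reported loss, so it will probably not run, although loss near 10% could overturn a modest effect

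*Protocol article*

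**What the plan says.** All in the Protocol article:

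- **Inferential Analysis, assumption:** "Missing primary outcomes will be assumed to be missing at random".
- **Inferential Analysis, check:** "if more than 15% of all primary outcomes that should be available for analysis are missing, a sensitivity analysis will be undertaken". The threshold applies to all primary outcomes together, not to each arm.
- **Inferential Analysis, primary test:** "The primary analysis will be to detect a difference in proportions using an unadjusted binomial test".
- **Inferential Analysis, additional models:** "generalized linear regression models for the analysis of binary outcomes will be used to study the effects of the intervention". Confounders enter where judged necessary. Marital status is among the examples, and adjusted relative risk and risk difference are to be reported.
- **Sample Size:** 1188 men, 594 per arm, including 10% inflation for loss; control event rate 60%, a 10% reduction, 90% power, alpha .05.
- **Results:** enrolment is complete, and "Follow-up of enrolled participants is ongoing. Loss to follow-up is under 10" per cent.
- **Follow-Up Procedures:** "If he is not located, he is considered lost to follow-up".
- **Other Substudies:** a nonresponse study, with no loss threshold, "comparing answers to a smaller number of questions (on exposure and outcome) of those lost to follow-up with those who remained".

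**The concern.** A rule for checking a missing-data assumption should apply at the loss the trial expects. This one starts at one and a half times that loss. Because it pools the arms, it also does not respond to an imbalance between them, which is the pattern that biases a comparison.

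The setting makes informative loss plausible. The outcome is self-reported sex against medical advice. Only the intervention men receive 38 messages about recovery and abstinence, and the Limitations section accepts that the messages may change what men report. They might equally change who comes back. If men who had sex return less often, and more so in the intervention arm, the observed difference overstates the benefit, and the stated plan need not show it.

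The second issue is how the assumption fits the test. The protocol calls its main analysis a missing-at-random analysis, but the unadjusted test uses no covariates. The adjusted model, which could carry that assumption, is only additional and is not linked to it.

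**Working it through.** **1. The plan's sample size.** Inputs: 60% v 50%, 90% power, alpha .05 (two-sided assumed; the article does not say).
n = [1.960·√(2·0.55·0.45) + 1.282·√(0.60·0.40 + 0.50·0.50)]² / 0.10² = 519 per arm; 519/0.9 = 577, total 1154. With continuity correction n = 538; 538·1.1 = 592 (total 1184) or 538/0.9 = 598 (total 1196). The stated 1188 is reproduced within 3%. A relative 10% reduction (60% v 54%) would need over 2500 men, so the design effect is read as 10 points. With 535 observed per arm (594 less 59) power is still 90.9%, so the issue is bias and not power.

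**2. The trigger.** Assuming 1188 enrolled:
- More than 15%: 0.15·1188 = 178.2, so at least 179 missing.
- Under 10%: at most 118.
- Gap: 179 − 118 = 61 further missing outcomes, about 61/1070 = 5.7% of the men followed up.
- As a limiting case of pooling, all 178 permitted missing outcomes could fall in one arm (178/594 = 30%) without the rule firing.

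**3. Tipping points at 10% loss.** Assumptions: 535 observed per arm, 10% missing, missing controls at the observed control rate, missing intervention men at the observed rate plus δ. The completed intervention rate is 0.9·p + 0.1·(p + δ) = p + 0.1·δ. Pooled z with n = 535:

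| Observed | z | p | δ at which z = 1.96 |
|---|---|---|---|
| 60% v 53% | 0.07/0.0303 = 2.31 | 0.021 | 0.107 |
| 60% v 52% | 0.08/0.0303 = 2.64 | 0.008 | 0.207 |
| 60% v 50% | 0.10/0.0304 = 3.29 | 0.001 | 0.407 |

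Each row reaches z = 1.96 at a completed intervention rate of 54.07%. If the standard error uses all 594 men per arm, the first and last shifts become about 14 and 44 points.

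Direct counts (59 missing per arm, n = 594, missing controls at 60%):
- 60% v 53%, with 70% of missing intervention men having had sex: (0.53·535 + 0.70·59)/594 = 54.7%; difference 5.3 points, p = 0.064.
- 60% v 50%: at 70% the difference is 8.0 points (p = 0.005), at 80% it is 7.0 points (p = 0.015), and at 100% it is 5.0 points (p = 0.079).

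**4. Unadjusted test under missing at random given marital status.** Assumed values, not from the article: 40% married, event risk 80% married and 46.7% unmarried (overall 60%), no treatment effect, 10% loss in each arm.
- Intervention loss 20% married and 3.3% unmarried: observed rate (0.32·0.80 + 0.58·0.467)/0.90 = 58.5%.
- Control loss 10% in both groups: observed rate 60.0%.
- Spurious benefit 1.5 points; type I error about 7.8%.
- Extreme pattern (25% and 0% v 0% and 16.7%): 3.7 points; type I error about 23%.
- Same marital pattern of loss in both arms, or loss depending on arm alone (12% v 5%): bias 0.

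**The case against.** Several stronger conclusions are tempting, and the article does not support them.

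- **That the trigger cannot fire.** It counts missing primary outcomes, whereas loss to follow-up is defined as not being located. A man who is located but declines, or who leaves the item blank on a self-administered paper form (Data Collection), is missing but not lost, and follow-up was still running. The trigger is unlikely to fire, not impossible.
- **That missing outcomes go unexamined.** The nonresponse substudy compares outcome answers whatever the loss. This lessens the concern. It does not remove it, because the substudy reaches only men who can be contacted and is not tied to the primary estimate.
- **That the unadjusted test is invalid under missing at random.** It is unbiased if loss depends on arm alone, or on covariates equally in both arms with a constant risk difference. The planned adjusted model already foresees marital status. What stands is that the test is not generally valid under that assumption and that the adjusted model is not named as the analysis carrying it.
- **That any significant result is fragile.** At the design effect, missing intervention men would need an event rate of about 91% with missing controls unshifted. Equal shifts in both arms leave the difference as observed when loss is equal.
- **That the status of telephone respondents is contradictory.** The substudy speaks of answers from men lost to follow-up, while Follow-Up Procedures counts only men not located as lost. This may be loose wording in a condensed article; nothing excludes telephone answers from the primary data.

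It is also fair that the choice of imputation method and similar detail belong in a fuller plan that is not shown. The trigger is different, because the article states it as a rule.

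**Conclusion.** The concern holds in a limited form. The only missing-data sensitivity analysis stated for the primary outcome has a threshold above both the planned and the reported loss, so on those figures it will probably not run. Loss near 10% is enough to overturn a modest effect: about 11 points of shift for 60% v 53% (14 with the larger denominator). It is not enough to threaten the design effect short of a shift of about 41 points. These figures assume equal 10% loss in the two arms, a shift in the intervention arm only, and a two-sided 5% test. The mismatch between the unadjusted test and the missing-at-random assumption matters only when covariate-related loss differs by arm or the effect varies with the covariate. In the illustrations it gives 1.5 to 3.7 points of bias, the upper figure from a deliberately extreme pattern. Severity is moderate. The article does not justify calling the primary test wrong or replacing it.

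**What to change.** 1. Delete the 15% trigger and always run the sensitivity analysis on the primary outcome.
2. Let the missing-outcome assumptions differ by arm, for example a delta-adjusted tipping-point analysis. The nonresponse substudy answers can inform the deltas, as guidance and not as limits, since men who could not be reached are absent from them.
3. Report missing primary outcomes and loss to follow-up by arm.
4. Keep the unadjusted test as primary. Name the already planned covariate-adjusted model, with marital status always included, as the supporting missing-at-random analysis.

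The cost is revised wording and a few extra analyses of data already collected, with no further participants. The article reports no interim analysis, so on what it states the change could be made without knowledge of results.

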### Other Substudies

There is a substudy embedded in the follow-up survey at 42 days which looks at how the study population reacts to the mobile system. The purpose is to evaluate the level of learnability and feasibility for the user in real life. This includes responsiveness to messages. Another study of nonresponse will be conducted comparing answers to a smaller number of questions (on exposure and outcome) of those lost to follow-up with those who remained in the cohort.

### Ethics and Dissemination

#### Ethical Issues

The three fundamental principles of research ethics—respect, beneficence, and justice—will be upheld through the use of an approved informed consent form, a completely confidential enrollment procedure and documentation system, and thorough ethical training and certification of all research staff that come in contact with participants. HIV results will be linked to individuals through a coded system. No interviewer will have access to an individual’s HIV test results. The phone messages will only be accessible by the intended recipient, who will be given a password. Thus, there is no potential for accidental revealing of the patient’s VMMC or HIV status or participation in the study. The study was approved by the Health Research Ethics Committee of Stellenbosch University (ref N14/08/108) and is registered in the Pan-African Clinical Trial Registry [PACTR201506001182385].

#### Informed Consent

The informed consent will be administered either one-on-one with the participants or in a group format. The group format will be followed up by a one-on-one session before signing. This consent process will be administered by a trained study recruiter. The staff member will offer to read the informed consent word-for-word to the participant. If the participant declines the offer, the staff member will give the participant ample time to read the consent form. When the participant has read the consent form, the staff member will go over the essential elements contained within. If the participant declines to read, all aspects of the informed consent will be reviewed in a language understood by the participant (English or Afrikaans). As part of the consent processes, the staff member will ask a series of open-ended questions to assess the participant’s understanding of the consent. If they fail to get more than 80% of the answers right, they will be asked to read the informed consent form once again; the recruiter can then focus on the issues that they answered incorrectly and try to clarify the information. Once the above procedure has been completed successfully, the study recruiter will read out the signature page to each participant before they sign the form. A copy of the signed form will be given to the participant.

#### Quality Control

Standard operating procedures were developed and key staff were trained formally in clinical research standards. A clinical monitoring visit was conducted by an external consultant and adaptations were made thereafter. All fieldworkers received training on good clinical practices.

#### Dissemination

Two publications from the development of the intervention are planned, and at least three publications on the effectiveness of the intervention and the substudies described above are planned. Results from the study will be published within three years of study completion in Creative Commons and open-access journals. The data will be owned by Stellenbosch University and protected under South African law. A description of the project and the variables will be provided to Swedish National Data Service, where the data will be stored.

## Results

Enrollment was completed on June 29, 2016. Follow-up of enrolled participants is ongoing. Loss to follow-up is under 10%. No interim analyses have been conducted.

## Discussion

### Summary

This trial will test a novel intervention developed with a participative, theory-based approach. If it is found to be effective, the intervention should have application to other areas of health care, particularly where human resource shortages are chronic.

### Limitations

There could be some response bias due to social desirability, meaning that those who got the messages may be more likely to report they did not have sex than those who did not get the messages (because they have been reminded repeatedly, not necessarily because they did not have sex). Additionally, the participant could potentially have healed completely before the official 6-week postoperative period ended, which would mean that penetrative sex was theoretically clinically safe. A patient could also unintentionally report his allocation status to a nurse during a clinical follow-up visit, thus contaminating the blinding. Finally, there is a possibility that going through the male circumcision procedure may disinhibit men from practicing safe sex such as using condoms with casual partners. The original study protocol included a 6-month follow-up to study the effects of the intervention on such risk compensation. However, funding did not allow for this and this arm was removed. Future studies should include such aspects where possible.

## Abbreviations

HISP: Health Information Systems Program
RCT: randomized controlled trial
UNAIDS: Joint United Nations Programme on HIV/AIDS
VMMC: voluntary medical male circumcision
WHO: World Health Organization
